#### **4.4.3 Alternative Therapies during the Double-blind Phase**

**The following regimens will be permitted:**

- Hydroxyurea therapy, if stable for at least 1 month preceding randomization and throughout the trial (no change in dose, except decrease for safety reasons)
- Long term oxygen therapy, if stable for at least 2 weeks prior to randomization
- Chronic blood transfusions, if started within at least 1 month preceding randomization and continued throughout the trial. Each efficacy assessment must occur at least 1 week before or at least 1 week after each chronic blood transfusion.
- Anticoagulants should be continued during the whole study period, if ongoing at time of entry into MIT
- ACE inhibitors, beta blockers, vasodilators (not including nitrate-based), diuretics provided they have been stable on the medication at least one month prior to enrollment in the study

Both the initiation of hydroxyurea therapy to those naïve to that treatment and tonsillectomy surgery should be delayed until conclusion of the double-blind phase of the MIT, unless deemed clinically necessary in the opinion of the investigator. Those subjects requiring either therapy during the MIT may, however, remain on study.

**The following regimens are forbidden:**

- Specific treatments for pulmonary hypertension (excluding acute administration during a catheterization procedure to test vascular reactivity)

- Protease inhibitor treatment for HIV
- Initiation of potent CYP3A4 inhibitor therapy (e.g., itraconazole, ritonavir, ketoconazole)
- Initiation of Chronic elective transfusion therapy during the double-blind phase of the MIT

See Section 7.1 for further information on study discontinuation for subjects requiring any of these forbidden therapies.

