### **5.3.2 Exclusion Criteria**

1. Current pregnancy or lactation
2. Any one of the following medical conditions:
  - Stroke within the last six weeks
  - New diagnosis of pulmonary embolism within the last three months
  - History of retinal detachment or retinal hemorrhage in the last 6 months
  - Non-arteritic anterior ischemic optic neuropathy (NAION) in one or both eyes
  - History of sustained priapism requiring medical or surgical treatment, unless currently impotent or on transfusion program within the last two years
  - Any unstable (chronic or acute) condition that in the opinion of the investigator will prevent completion of the study
3. Subjects taking nitrate-based vasodilators (including, but not limited to nicorandil [available in the UK only] ), prostacyclin (inhaled, subcutaneous or intravenous) or endothelin antagonists. Subjects taking calcium channel blockers will be allowed to participate provided they are on a stable dose for  $\geq 3$  months.
4. Left ventricular ejection fraction  $< 40\%$  or clinically significant ischemic, valvular or constrictive heart disease: LVEF  $< 40\%$  or SF  $< 22\%$
5. Subjects who are in other research studies with investigational drugs, with the exception of hydroxyurea, unless the other trial has been approved by the walk-PHaSST Executive Committee for co-participation
6. Acute or chronic impairment (other than dyspnea), limiting the ability to comply with study requirements (in particular with 6MWT), e.g., angina pectoris, intermittent claudication, symptomatic hip osteonecrosis
7. Tonsillectomies for sleep apnea within 3 months prior to randomization
8. Active therapy for pulmonary hypertension, including prostacyclin analog, endothelin-1 antagonists, or PDE-5 inhibitor
9. Protease inhibitor therapy for the treatment of HIV

10. Subjects taking potent CYP3A4 inhibitor therapy (e.g., itraconazole, ritonavir, ketoconazole)
11. Subjects who are anticoagulated **and** have proliferative retinopathy (unless they have had ophthalmologist recommended intervention (e.g., phototherapy) or have been otherwise cleared by an ophthalmologist to participate in the study)
12. Subjects with systolic blood pressure greater than or equal to 140 mmHg OR diastolic blood pressure greater than or equal to 90 mmHg. See Section 9.3.3 for qualifying blood pressure assessment instructions.

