## **7 MONITORING OF SUBJECTS AND CRITERIA FOR WITHDRAWAL OF SUBJECTS**

### **7.1 Subject Discontinuation**

Therapy will be discontinued for the following reasons:

1. Major bleeding complication including intracerebral hemorrhage or stroke, GI hemorrhage, need for major surgery.
2. One episode of severe priapism defined as priapism lasting for more than 4 hours or requiring transfusion or surgical therapy (see Section 4.4.2.3 for further details of priapism monitoring)

3. Positive quantitative blood HCG or pregnancy
4. New retinal detachment, hemorrhage or clinically significant visual change (Subjects will be instructed by site personnel to alert their local CI of any visual changes between study visits; the CI will schedule an immediate evaluation by an ophthalmologist if a randomized subject complains of changes in vision.)
5. Serious adverse events considered to be related to the study drug
6. Introduction of specific treatments for pulmonary hypertension (excluding acute administration during a catheterization procedure to test vascular reactivity)
7. Initiation of chronic transfusion therapy (in this instance, EOS assessments should occur either immediately prior to initiation of transfusions or between 2-3 weeks after the transfusion)
8. Protease inhibitor treatment for HIV
9. If an emergency clinical unblinding of treatment assignment is required
10. Initiation of potent CYP3A4 inhibitor therapy (e.g., itraconazole, ritonavir, ketoconazole)

Sickle cell related clinical deterioration, other than those requiring initiation of chronic transfusion therapy, does not require withdrawal of study medication. Likewise, clinical deterioration of PH does not necessarily require discontinuation of study medication, unless the Investigator feels it is necessary to introduce another PH medication. In any situation where subject discontinuation is not required, the Investigator may always choose to discontinue the subject based on his or her clinical judgment. Any premature discontinuation of study drug precludes participation in the Open-Label Follow-up Phase of the MIT. At the time of study drug discontinuation all EOS visit assessments should be obtained to the extent possible. Such subjects should continue to be followed for adverse events and collection of other study data to the extent possible. Assessment of study endpoints should be made blinded to subjects' study treatment as much as possible.

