## **7.2 Dose Modification or Discontinuation Due to Expected Adverse Events: Headache or Facial/skin Edema**

Dose adjustment instructions for symptomatic/dose limiting headache or facial/skin edema sufficient to warrant discontinuation of the drug (only for symptoms that are severe enough as described by subject or physician to warrant holding the drug) are provided herein.

1. If present during initial dose (20 mg) hold for one day and rechallenge, if symptoms occur upon rechallenge discontinue drug. Data collection should continue for such subjects to the extent possible.

2. If present during dose escalation (40 or 80 mg) hold drug for one day and restart at previously tolerated dose for one week. If symptoms recur, discontinue drug but continue to follow subject for collection of safety and other data. If tolerated for one week increase dose to desired level as dictated by protocol. If symptoms recur upon second increase hold drug for one day and drop dose to previously tolerated dose for the duration of the trial.

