### 9.2.4 Clinical Outcome Adjudication

A subset of clinical outcomes that occur during the randomized, double-blind phase will be adjudicated by a blinded panel of experts. Adjudicated outcomes include: ACS, right heart failure, and clinical deterioration of PH.

In order to determine clinical deterioration of PH, the adjudication panel will consider, at a minimum, the following:

- 20% decrease in six-minute walk distance, on two successive evaluations taken at least 2 weeks apart while not in VOC, plus deterioration in NYHA/WHO functional class
- Initiation of additional PH specific therapy, that is, prostanoid analogue, endothelin receptor antagonist or PDE 5 inhibitor

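### Nitrates are barred at entry, but starting one during the double-blind phase triggers no mandatory stop, hold or titration freeze

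*Protocol*

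**What the plan says.** Nitrates come up twice in the rules on who may take what.

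- **Section 5.3.2, exclusion 3**, bars at entry "Subjects taking nitrate-based vasodilators (including, but not limited to nicorandil" and similar agents.
- **Section 4.4.3, permitted regimens**, allows "ACE inhibitors, beta blockers, vasodilators (not including nitrate-based), diuretics provided they have been stable on the medication at least one month prior" to enrollment.

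The forbidden regimens in 4.4.3 are four: "Specific treatments for pulmonary hypertension (excluding acute administration during a catheterization procedure to test vascular reactivity"), protease inhibitors for HIV, starting a potent CYP3A4 inhibitor, and starting chronic elective transfusion. The list closes with a pointer: "See Section 7.1 for further information on study discontinuation for subjects requiring any of these forbidden therapies".

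Section 7.1 gives ten reasons for which therapy will be discontinued. The four forbidden regimens all reappear there, for example "Initiation of potent CYP3A4 inhibitor therapy (e.g., itraconazole, ritonavir, ketoconazole" as item 10. Section 7.1 also says that, where a stop is not required, "the Investigator may always choose to discontinue the subject based on his or her clinical judgment".

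Section 7.2 contains the only hold and step-down rules. Its scope is "Dose adjustment instructions for symptomatic/dose limiting headache or facial/skin edema sufficient to warrant discontinuation of the drug".

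**The concern.** The protocol judges that a patient already on a nitrate should not be given sildenafil in this trial. The same combination can arise after randomization, when a nitrate is started during treatment. For the other drug classes barred at entry, the protocol foresees this and requires a stop. For nitrates it requires none.

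The stake is patient safety. Section 8 lists hypotension among the potential adverse events of sildenafil. Section 13.7.2 anticipates, under sildenafil, hypotension needing admission or fluids and hypotension needing vasopressors. Dose escalation is scheduled and carries no condition about concomitant nitrates. Sites do not ordinarily know who is on active drug, so the workable safeguard is a single stated action that applies to every subject.

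**Working it through.** The protocol gives no figure to reproduce here. The check is a comparison of lists, followed by simple arithmetic on the dose schedule.

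**1. Where each class barred at entry goes.** Exclusions 3, 8, 9 and 10 name six drug classes.

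| Class barred at entry | Exclusion | 4.4.3 forbidden list | 7.1 stopping list |
|---|---|---|---|
| Prostacyclin and analogs | 3, 8 | yes, as PH treatment | yes, item 6 |
| Endothelin antagonists | 3, 8 | yes, as PH treatment | yes, item 6 |
| PDE-5 inhibitors | 8 | yes, as PH treatment | yes, item 6 |
| HIV protease inhibitors | 9 | yes | yes, item 8 |
| Potent CYP3A4 inhibitors | 10 | yes | yes, item 10 |
| Nitrate-based vasodilators | 3 | **no** (0 of 4 items) | **no** (0 of 10 items) |

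Five of six are carried into both lists; nitrates are in neither. Counted by list entry, with the three PH classes taken as one, three of four are carried over and the exception is the same. Exclusion 5 (other investigational drugs) is also not repeated, but it names no class and can be waived by the Executive Committee. The point is therefore not that the lists must match item by item.

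**2. Could nitrates come in as PH treatment?** Section 9.2.4 spells the term out: "Initiation of additional PH specific therapy, that is, prostanoid analogue, endothelin receptor antagonist or PDE 5 inhibitor". Exclusion 8 names the same three classes as active PH therapy. Neither includes nitrates, and exclusion 3 names nitrates separately.

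**3. Could they come in through the permitted list?** That list shows that nitrates are not permitted. But its vasodilator entry concerns background medication that was stable before enrollment, and it attaches no consequence. The pointer to 7.1 covers only the forbidden list.

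**4. Could they come in through 7.2?** No. Its holds and reductions are for headache and facial or skin edema.

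**5. What remains in 7.1.** Investigator discretion, which is optional; item 5, a serious adverse event related to study drug, which acts after harm; and item 9, emergency unblinding.

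**6. Dose during the exposure window (section 4.4.2.4).**

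- Weeks 1–6: 3 × 20 = 60 mg/day
- Next 4 weeks: 3 × 40 = 120 mg/day
- Last 6 weeks: 3 × 80 = 240 mg/day
- Time above the starting dose: 4 + 6 = 10 of 16 weeks
- Final dose relative to starting dose: 240 / 60 = 4

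**7. Who can be exposed.** Section 11.6 plans 132 subjects, 66 of them on sildenafil. Only those 66 can have the combination in the double-blind phase.

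**The case against.** The strongest reply is that nitrates are already disallowed. A nitrate started on study fails both conditions of the permitted vasodilator entry, so it is a protocol deviation, and section 13.10.3 requires deviations to be reported with any corrective action. Section 6 also allows emergency unblinding when the treating team needs to know the drug, and 7.1 item 9 then forces a stop. This is true, and it narrows the gap: what is missing is a required treatment action, not the restriction itself. Deviation reporting does not stop or hold drug, however, and unblinding covers only acute need.

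Second, the definition in 9.2.4 was written for adjudicating clinical deterioration, and exclusion 8 uses open wording. That is fair, but reading nitrates into PH treatment remains strained when exclusion 3 lists them separately.

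Third, the protocol gives no reason for exclusion 3 and describes no interaction between sildenafil and nitrates; limiting confounding could be the motive. This stands as a limit on severity. The argument here rests on the protocol's own entry bar and its own recognition of hypotension, not on interaction data.

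Fourth, new nitrate use should be uncommon, since exclusions 4 and 6 remove clinically significant ischemic heart disease and limiting angina. That also stands. The dose arithmetic describes the schedule and says nothing about how many subjects would be affected.

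Finally, a temporary hold might be enough after a brief nitrate exposure. That is a reasonable alternative; the essential point is that some action be stated.

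**Conclusion.** The gap is real. Starting a nitrate on study is outside the permitted regimens but leads to no mandatory stop, hold or titration freeze, whereas PH-specific therapy, HIV protease inhibitors and potent CYP3A4 inhibitors each lead to mandatory discontinuation. This looks like an oversight in carrying drug exclusions through to the treatment phase, and it should be fixed.

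The list comparison is certain on the text. The clinical consequence is less so: the protocol gives neither the frequency of new nitrate use, which is probably low, nor any data on the combination. The conclusion also assumes that the Manual of Operations, which is not at hand, does not supply the missing rule; the protocol does not refer to it for nitrates.

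**What to change.** Add the initiation of any nitrate-based vasodilator or nitric oxide donor, including nicorandil, to the forbidden regimens in 4.4.3 and to the reasons for stopping therapy in 7.1. Exempt the inhaled nitric oxide given at catheterization under Table 2. Naming nitric oxide donors goes slightly beyond exclusion 3, which is why the exemption has to be explicit.

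The cost is one line in each list. Concomitant medications are already reviewed at Weeks 6, 10 and 16, so no new data collection is needed. The downside is that a few subjects, some of them on placebo, may have to stop study drug, and under 7.1 a premature stop also bars them from the Open-Label Follow-up Phase. If the sponsor finds that too harsh for brief nitrate use, a mandatory hold with no dose escalation, written into 7.2, would be the lesser alternative.

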#### **4.4.4 Open-Label Follow-up Phase**

After the completion of the 16-week randomized phase, patients will be offered open-label sildenafil for up to 1 year. Sites will maintain clinical outcome follow-up with these patients during this time, every 1-3 months, based on each site's standard practice. To preserve the scientific integrity of the MIT, all subjects will remain blinded to their MIT treatment assignment until after the MIT database is locked. In order to maintain the blind on a per subject basis and to minimize the possibility of sildenafil related adverse effects, at the beginning of the Open-label Follow-up Phase all patients will be down titrated from 80mg TID of sildenafil or placebo to 20 or 25mg of sildenafil TID. The doses will then be titrated upward as tolerated (see section 7.2 for dose adjustment guidelines in case of adverse effects). Doses will increase by 20-25mg TID every two weeks, but a faster dose escalation regimen will be allowed if, in the opinion of the treating clinician, a patient has become symptomatic due to apparent dose down-titration. The maximum dose will either be 75 mg or 80 mg TID, depending on 20 mg or 25 mg tablet availability. During the course of this year, the CI and administrative team will make every effort to assist patients in obtaining medication from a non-study source; this could include, for instance, helping obtain insurance coverage for their drug. Patients will be informed that these efforts do not guarantee availability of open label drug at the end of the study contract.

Adverse events and study drug dosing schedules will be collected during this open-label period.

If patients choose not to participate in the Open-Label Follow-up Study, they will be required to return to the clinic for a one-month safety follow-up visit approximately 30 days after the MIT Week 16 visit. Clinical Investigators will taper study drug for these non-continuing patients upon completion of the MIT treatment phase. The taper will continue for 3-7 days, based on CI judgment; blinded study medication will be provided in a quantity sufficient to supply the maximum taper period. Tapering is not recommended for patients requiring discontinuation of the drug due to AEs.

Refer to Chapter 13.3 of the MOO for a suggested taper regimen and for additional details.

## **5 SELECTION OF SUBJECTS**

Eligibility will be based on the following inclusion and exclusion criteria.

### **5.1 Screening Phase**

#### **5.1.1 Inclusion Criteria**

1. Males or females, 12 years of age or older
2. Diagnosis of sickle cell disease (including, but not limited to SS, SC, SD, or S $\beta^{\circ}$ /+ thalassemia)
3. Provision of informed consent and, where applicable, assent

### **5.2 Observational Follow-up Study**

#### **5.2.1 Inclusion Criteria**

1. Satisfaction of screening criteria
2. In the opinion of the investigator, ability to maintain follow-up contact
3. Failure to satisfy the eligibility requirements of the MIT OR discontinuation/completion of the MIT/Open-label Follow-up Phase
4. Provision of informed consent and, where applicable, assent

### **5.3 Main Interventional Trial**

#### **5.3.1 Inclusion Criteria**

1. Males or females, greater than or equal to 12 years of age and less than or equal to 70 years of age
2. For female subjects, on a reliable method of birth control or not physically able to bear children
3. Electrophoretic documentation of sickle cell disease (including, but not limited to SS, SC, SD, or S $\beta^{\circ}$ /+ thalassemia)
4. At least mild pulmonary hypertension with TRV  $\geq 2.7$  m/s by echocardiogram
5. Six minute walk distance of 150-500 m
6. In the opinion of the investigator, ability to complete the protocol scheduled assessments during the 16 week, double-blind phase
7. Provision of informed consent and, where applicable, assent

8. Subjects with systemic hypertension must be on a stable antihypertensive regimen for greater than or equal to 90 days and a stable dose for greater than or equal to 30 days.

### **5.3.2 Exclusion Criteria**

1. Current pregnancy or lactation
2. Any one of the following medical conditions:
  - Stroke within the last six weeks
  - New diagnosis of pulmonary embolism within the last three months
  - History of retinal detachment or retinal hemorrhage in the last 6 months
  - Non-arteritic anterior ischemic optic neuropathy (NAION) in one or both eyes
  - History of sustained priapism requiring medical or surgical treatment, unless currently impotent or on transfusion program within the last two years
  - Any unstable (chronic or acute) condition that in the opinion of the investigator will prevent completion of the study
3. Subjects taking nitrate-based vasodilators (including, but not limited to nicorandil [available in the UK only] ), prostacyclin (inhaled, subcutaneous or intravenous) or endothelin antagonists. Subjects taking calcium channel blockers will be allowed to participate provided they are on a stable dose for  $\geq 3$  months.
4. Left ventricular ejection fraction  $< 40\%$  or clinically significant ischemic, valvular or constrictive heart disease: LVEF  $< 40\%$  or SF  $< 22\%$
5. Subjects who are in other research studies with investigational drugs, with the exception of hydroxyurea, unless the other trial has been approved by the walk-PHaSST Executive Committee for co-participation
6. Acute or chronic impairment (other than dyspnea), limiting the ability to comply with study requirements (in particular with 6MWT), e.g., angina pectoris, intermittent claudication, symptomatic hip osteonecrosis
7. Tonsillectomies for sleep apnea within 3 months prior to randomization
8. Active therapy for pulmonary hypertension, including prostacyclin analog, endothelin-1 antagonists, or PDE-5 inhibitor
9. Protease inhibitor therapy for the treatment of HIV

10. Subjects taking potent CYP3A4 inhibitor therapy (e.g., itraconazole, ritonavir, ketoconazole)
11. Subjects who are anticoagulated **and** have proliferative retinopathy (unless they have had ophthalmologist recommended intervention (e.g., phototherapy) or have been otherwise cleared by an ophthalmologist to participate in the study)
12. Subjects with systolic blood pressure greater than or equal to 140 mmHg OR diastolic blood pressure greater than or equal to 90 mmHg. See Section 9.3.3 for qualifying blood pressure assessment instructions.

### 5.3.3 Randomization Criteria

1. Second 6MW distance between 150-500 meters and within 15% of the previous 6MW (Refer to Section 9.2.3)
2. Second echocardiogram with a TRV  $\geq 2.7$  m/s
3. For subjects undergoing right heart catheterization, pulmonary capillary wedge pressure  $\leq 24$  mmHg
4. An ophthalmological exam sometime within the past year for patients not being anticoagulated. A completed baseline ophthalmological exam for patients being and who otherwise qualify (see Exclusion Criteria #11)

## 6 RANDOMIZATION AND BLINDING

The study will randomize 132 subjects.

After successful qualification of their baseline data and the completion of the RHC procedure (for subjects with TRV  $\geq 3.0$ ), subjects will be randomized to one of two treatment arms by the internet based, secure RhoRAND™ system provided by the Data Coordinating Center (DCC). Subjects in Arm 1 will receive sildenafil. Subjects in Arm 2 will receive oral placebo. A computer-generated, adaptive randomization schema will be used to allocate subjects 1:1 between the two treatment arms. Randomization will be stratified by site and TRV stratum ( $2.7 \text{ m/s} \leq \text{TRV} < 3.0 \text{ m/s}$  versus  $\text{TRV} \geq 3.0 \text{ m/s}$ ). As the number of stratification factors is rather large ( $9 \times 2 \times 2$ ), many strata may have fewer subjects than the block size, and a good balance can no longer be guaranteed for all of them^34. As a result, the use of a traditional stratified, blocked randomization schedule could lead to significant imbalance in treatment allocations, both across the study and within the various strata. In order to increase the likelihood of balance in treatment allocations, subjects will be randomized using the standardized range variation of the sequential allocation algorithm of Pocock and Simon, a minimization method. This method attempts to achieve treatment balance on several subject characteristics (i.e., site and TRV stratum in this study) simultaneously – not within separate strata. Minimization

consists of biasing the treatment allocation so as to minimize the total imbalance between the treatment groups on some scale. The order of entry of the subjects to the various sites and in the various prognostic groups is assumed to be random. As minimization is a dynamic method that uses information on subjects already entered to allocate treatment to the next subject, and thus a continuous updating of the information related to previous treatment allocations is required, a centralized randomization system will be used.

The unmasked statistician will monitor the balance of treatment assignments across subjects on anticoagulants (defined as vitamin K antagonists and heparin). If a significant imbalance is detected, anticoagulant use will be added as stratification factor in the randomization.

RhoRAND will be configured to send alerts to the project administrative team when numbers in a stratum approach 66. Based on power calculations, a minimum of 64 subjects with  $TRV \geq 3.0$  m/s should be randomized. Additionally, slight over-enrollment in the  $2.7 \text{ m/s} \leq TRV < 3.0 \text{ m/s}$  stratum may be permitted by NHLBI, if funding is available at that time.

To preserve the scientific integrity of the MIT, all subjects will remain blinded to their MIT treatment assignment until after the MIT database is locked.

Pharmacists at each site will be blinded and will utilize the blinded randomization notification from RhoRAND to issue appropriate study drug to each randomized subject. The RhoRAND system is able to provide unblinding information in case of a medical emergency where the exact study drug is needed in order to appropriately treat a subject. This information can only be accessed by a pre-authorized individual, such as the medical monitor.

The subjects, physicians, nurses, and ancillary support staff will be blinded to individual treatment assignment. The placebo formulations will be identical in appearance and taste to the active compounds (see Section 8.1).

The mechanism for unblinding in a clinical emergency will be detailed in the Manual of Operations.

